## Abstract

**Background:**

Tuberculosis-associated obstructive pulmonary disease (TOPD), recognized as a high-morbidity respiratory condition in most countries, presents significant clinical challenges in differential diagnosis and comorbidity management, while substantially elevating all-cause mortality risk. Preclinical investigations of Yiqi Gubiao Pill (National Patent ZL201410536529.5) have demonstrated multi-target therapeutic efficacy, including cough suppression, bronchospasm alleviation, sputum expectoration facilitation, and disease progression retardation. This randomized controlled trial aims to systematically assess Yiqi Gubiao’s therapeutic and evaluate its safety.

**Methods:**

We will implement a prospective double-blind randomized controlled trial utilizing 1:1 allocation ratio, randomly assigned to either the Yiqi Gubiao pill treatment group or placebo-controlled group. Following randomization, a standardized 12-week therapeutic protocol will be administered, during which serial pulmonary function assessments and quality of life evaluations will be conducted. Concurrently, validated Traditional Chinese Medicine (TCM) symptom scoring scales will be applied for score. Systematic safety surveillance will be performed through weekly monitoring of adverse events.

**Discussion:**

This prospective, double-blind, randomized clinical trial will provide valuable data on the efficacy and safety of Yiqi Gubiao pill in treating TOPD. Positive results will offer a new treatment option for patients with TOPD.

**Clinical Trial Registration:**

[ClinicalTrials.gov], identifier [NCT06676800]. Registered 30 October 2024, https://ClinicalTrials.gov.

## 1 Introduction

According to the latest World Health Organization (WHO) report, tuberculosis (TB) has surpassed HIV/AIDS as the leading global cause of death from infectious diseases. In 2021 alone, an estimated 10.6 million people worldwide contracted TB, resulting in 1.6 million fatalities (Bagcchi, 2023). Notably, pulmonary tuberculosis (PTB) constitutes 80%–90% of all active TB cases. Existing research confirms that *Mycobacterium tuberculosis* has infected one-third of the global population, with approximately 10% of these latent infections progressing to active disease during the infected individuals’ lifetime (Dheda et al., 2016).

As one of the 30 high-burden TB countries designated by WHO, China contributes 9% of global tuberculosis cases, ranking second worldwide and surpassed only by India (Wang et al., 2012). Epidemiological monitoring reveals Xinjiang as the region with the most severe PTB burden in China, demonstrating an incidence rate 2.58 times higher than the national average (He et al., 2018). This disparity stems from multiple systemic challenges in the region, including geographical constraints, socioeconomic disparities, inadequate healthcare infrastructure, insufficient public health education, and critical shortages in TB prevention specialists (Qi, 2016). These compounding factors have driven a persistent escalation of TB transmission, establishing it as the most pressing public health challenge in northwestern China.

Recent clinical observations have identified a significant comorbidity between PTB and chronic obstructive pulmonary disease (COPD). Patients manifesting this specific comorbidity are clinically classified as having Tuberculosis-Associated Obstructive Pulmonary Disease (TOPD), a distinct diagnostic entity recognized in respiratory medicine (Sarkar et al., 2017). Comparative cohort studies demonstrate that TOPD patients exhibit distinct clinical trajectories compared to non-PTB-associated COPD cases: earlier disease onset (mean age reduction of 7.2 years), accelerated mortality timelines (hazard ratio 1.89), elevated exacerbation frequency (2.3-fold increase in annual hospitalization rates), and significantly diminished 10-year survival probabilities (34% vs 61%) (Yakar et al., 2017).

Current international TB management guidelines (Nahid et al., 2016) endorse the first-line therapeutic regimen comprising rifampicin, isoniazid, pyrazinamide, and ethambutol (RIPE protocol), supplemented by oxygen therapy in cases of concurrent obstructive ventilatory impairment. However, extended administration of first-line anti-TB agents precipitates dual therapeutic challenges: cumulative drug resistance development and suboptimal COPD comorbidity control. Therapeutic escalation to second-line agents (fluoroquinolones, diarylquinolines, and nitroimidazole derivatives including moxifloxacin, bedaquiline, and pretomanid) becomes imperative for multidrug-resistant TB. Nevertheless, pharmacovigilance data reveal significant neurotoxicity and idiosyncratic hepatotoxicity associated with prolonged use (Johnson et al., 2024). This therapeutic dichotomy has revitalized interest in TCM as adjuvant therapy, with meta-analytical evidence demonstrating adjunctive TCM protocols significantly improve clinical outcomes through three principal mechanisms: (1) reduction of standard chemotherapy cycle (2) accelerated sputum culture conversion rates and (3) decreased recurrence risk. Furthermore, longitudinal studies reveal TCM’s immunomodulatory properties mediate sustained pulmonary rehabilitation, such as enhance patient immunity and improve lung function (Luo and Cai, 2019; Huang and Hu, 2017).

Yiqi Gubiao Pill, a hospital-developed botanical formulation (Preparation Approval No. ZJ20130098; National Invention Patent License ZL201410536529.5; NMPA Clinical Trial Authorization 2018L02421), demonstrates multimodal therapeutic properties in preclinical studies. Pharmacodynamic evaluations reveal its significant antitussive, antiasthmatic, mucoactive, and immunopotentiating effects, with mechanistic studies indicating Yiqi Gubiao Pill’s capacity to downregulate serum concentrations of pro-inflammatory cytokines (Li et al., 2016). Bronchodilatory effects are mediated through reduction in airway resistance (Raw) and upregulation of pulmonary aquaporin-1 (AQP1) expression, elucidating its molecular mechanism in respiratory pathophysiology. This clinical trial (ClinicalTrials.gov ID: NCT06676800) implements a prospective double-blind, placebo-controlled randomized clinical trial (RCT) design to evaluate both therapeutic efficacy and safety profile in treatment-naive adults with active PTB complicated by COPD. This evidence-based approach aims to establish optimized integrative management protocols for this high-risk patient cohort. Meanwhile, through this three-phase model of “local problem-driven, scientific method validation, global demand adaptation,” Xinjiang’s TB research outcomes can serve as a pivotal nexus connecting China’s expertise with global tuberculosis control initiatives.

## 2 Methods and analysis

### 2.1 Study design

This prospective double-blind randomized controlled trial, registered with the Clinical Trials (registration number: NCT06676800), will implement a 1:1 allocation design randomized to either the Yiqi Gubiao treatment group or placebo-controlled group. Following randomization, a 12-week therapeutic protocol will be administered, during which serial pulmonary function assessments and quality of life evaluations. TCM syndrome differentiation will be quantified through the validated TCM Symptom Score Scale, while safety surveillance will systematically monitor adverse events. The trial adheres to SPIRIT guidelines (Standard Protocol Items: Recommendations for Interventional Trials), with the completed checklist provided in Supplementary Material 1. The complete study workflow is detailed in Figure 1.

**FIGURE 1 F1:**
[figure not shown]
The flow chart of the experiment.

### 2.2 Study setting

Study participants meeting the diagnostic criteria for active PTB with comorbid COPD will be recruited from respiratory medicine outpatient clinics and inpatient wards at the Sixth People’s Hospital of Xinjiang Uygur Autonomous Region. Diagnostic confirmation of active PTB will adhere to the Chinese National Health Commission’s Health Industry Standard WS 288-2017, requiring: 1) radiological evidence of active TB lesions on chest CT, and 2) microbiological confirmation through acid-fast bacilli (AFB) smear positivity with subsequent *Mycobacterium tuberculosis* growth on culture medium. All enrolled subjects will provide written informed consent following approval by the Sixth People’s Hospital of Xinjiang Uygur Autonomous Region Medical Ethics Committee (Approval No. 2021XE0138).

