### 2.3 Participants

#### 2.3.1 Inclusion criteria

Patients who meet the following criteria will be included:1. Aged 40-75 years old;2. Meeting the Western medical diagnostic criteria and typing standards for active PTB;3. No use of steroids, anti-tuberculosis medications, or immunosuppressants, nor desensitization therapy administered within the past month;4. Documented comprehension of therapeutic protocols with voluntarily signed informed consent.

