#### 2.5.2 Conventional treatment

Both treatment and control groups receive standardized anti-tuberculosis therapy following the WHO-recommended RIPE regimen—an intensive 8-week phase with daily rifampicin, isoniazid, pyrazinamide, and ethambutol, followed by a 16-week continuation phase with rifampicin and isoniazid—and concurrently receive guideline-concordant COPD management, including maintenance bronchodilator therapy.

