### 2.7 Data collection and management

Data collection will be carried out before, during, and after treatment (Table 2). Data will be recorded on pre-designed case report forms (CRF) and transferred to an electronic format (RevMan 5.3) for storage and data backup. All patient identity information will be encoded.

**TABLE 2 T2:** Participant enrollment process, interventions, and outcome measures.

Items	Baseline	Treatment phase (monitor monthly)			Follow-up phase (monitor monthly)		
		1 month	2 months	3 months	3 months	6 months	12 months
Enrolment							
Recruitment	●						
Eligibility Screening	●						
Signed written informed consent	●						
Allocation	●						
Intervention							
Yiqi Gubiao pill (Treatment group)		●	●	●	●	●	●
Yiqi Gubiao pill Placebo (Control Group)		●	●	●	●	●	●
Outcomes							
forced vital capacity (FVC)	●	●	●	●	●	●	●
the percentage of FVC predicted (FVC%)	●	●	●	●	●	●	●
the percentage of forced expiratory volume in one second predicted (FEV1%)	●	●	●	●	●	●	●
FEV1/FVC	●	●	●	●	●	●	●
CAT score	●	●	●	●	●	●	●
mMRC score	●	●	●	●	●	●	●
BDI score	●	●	●	●	●	●	●
TDI score	●	●	●	●	●	●	●
chest X-ray/CT	●	●	●	●	●	●	●
Traditional Chinese Medicine Symptom (TCMS) score	●	●	●	●	●	●	●
Security							
All adverse events (including symptoms, signs, etc.)		●	●	●	●	●	●
Liver function: alanine aminotransferase, aspartate aminotransferase, total bilirubin, albumin, globulin	●	●	●	●	●	●	●
Renal function: uric acid, urea nitrogen, serum creatinine, β2-microglobulin, urinary protein, carbon dioxide binding rate, cystatin C	●	●	●	●	●	●	●

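### As printed, the culture requirement and the drug-free month together admit a newly diagnosed patient only if anti-TB treatment has not started by the time culture grows

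*Protocol article*

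**What the plan says.** Section 2.2 describes who is recruited: "Study participants meeting the diagnostic criteria for active PTB with comorbid COPD will be recruited from respiratory medicine outpatient clinics" and inpatient wards of one hospital. It then says what confirmation of active PTB requires: active lesions on chest CT, and "microbiological confirmation through acid-fast bacilli (AFB) smear positivity with subsequent" growth of M. tuberculosis on culture. No other route to the diagnosis is printed.

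Section 2.3.1 turns the diagnosis into an inclusion criterion (item 2: "Meeting the Western medical diagnostic criteria and typing standards for active PTB") and adds a drug-free window (item 3: "No use of steroids, anti-tuberculosis medications, or immunosuppressants, nor desensitization therapy administered within the past month"). The Introduction describes the trial as being "in treatment-naive adults with active PTB complicated by COPD".

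Section 2.5.2 sets the background treatment: "Both treatment and control groups receive standardized anti-tuberculosis therapy following the WHO-recommended RIPE regimen". It does not date the start of RIPE relative to smear, culture or allocation.

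**The concern.** Each rule is reasonable alone. A microbiologically confirmed diagnosis is sound, and so is a treatment-naive population. The difficulty lies in combining them when one part of the diagnosis arrives after another. Culture growth follows the smear, and the drug-free month counts back from entry. If culture growth is needed for entry, the whole smear-to-culture interval must have passed without treatment.

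Two things are at stake:

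- **Safety.** A patient who enters on the printed rules has had smear-positive disease untreated until culture grew. Nothing in the visible text guards against treatment being postponed to keep a patient eligible.
- **Recruitment.** A patient treated promptly on the smear is lost to a single-hospital trial that plans 74 participants.

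RIPE is given in both arms, so its start is not part of the randomised comparison. The rule acts before allocation and alike in both arms. The issue is therefore who can enter and in what condition, not bias between the arms.

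**Working it through.** No formula applies, and the plan gives no figure to reproduce. The check sets the rules side by side and runs each kind of patient through them.

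**Inputs**

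- R1 (2.2, applied through 2.3.1 item 2): CT lesions, positive smear and later culture growth, in patients who already meet the criteria when recruited.
- R2 (2.3.1 item 3): no anti-TB drug in the past month.
- R3 (Introduction): treatment-naive.
- Planned sample (2.4): 74 participants, 1:1, so 74 / 2 = 37 per arm.

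**Cases, for a patient with CT lesions and a positive smear**

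| Patient | R1 | R2 | R3 | Enters as printed? |
|---|---|---|---|---|
| A. RIPE started at the smear, still being taken when culture grows | met | fails | fails | no |
| B. Untreated, culture still pending | not yet met | met | met | no |
| C. Untreated when culture grows | met | met | met | yes |
| D. Treated earlier, stopped more than a month ago, culture grows | met | met | fails | no |
| E. Untreated, culture does not grow M. tuberculosis | fails | met | met | no |

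Only C enters. C includes a patient whose treatment was postponed. It also includes one who reached the hospital untreated with culture already grown, for whom the trial imposed no delay. The exact statement is therefore that treatment has not started by the time culture grows, whatever the reason.

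**What the link rests on.** Item 2 refers to Western diagnostic criteria without naming the definition in 2.2. Joining them is an inference, but 2.2 gives the only PTB definition in the article and says that recruited patients meet it.

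**Scope.** The definition covers all 74 participants, 37 per arm. The article gives neither the smear-to-culture time nor the share of patients started on RIPE at the smear, so no length of delay and no number of lost patients can be calculated.

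**Same cases after the fix below.** B becomes eligible at the smear, is allocated and starts RIPE at once. A becomes avoidable, because the patient can be allocated before the first dose. D stays excluded. E can be randomised, which is the price of the change.

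**The case against.** The strongest reply is that *subsequent* means after enrolment: the patient enters on CT and smear, and culture confirms later. That reading removes the problem, and when a laboratory result must be in hand is the sort of detail an article may leave to the full protocol. In addition, the workflow in Figure 1 is not visible and might show the order of events. This stands as a reason for caution about intent. It does not settle the text. *Subsequent* places culture after the smear and says nothing about allocation, while 2.2 recruits patients who already meet the criteria. On the benign reading, patients would be allocated before meeting an inclusion criterion, and no visible section allows that. The point therefore concerns a rule that is printed, not a missing detail.

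A second reply is that culture has value: it shows that the acid-fast bacilli are M. tuberculosis. That is right, and relaxing the entry rule is a trade-off.

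A third is that the harm depends on how long culture takes, which the article does not say. That is also right, and no size is claimed.

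A reader might infer more than the documents support:

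- *That the criteria contradict each other and nobody can enter.* Patient C can.
- *That the trial withholds treatment.* No section says RIPE is delayed or made conditional on culture, and a patient may arrive untreated with culture already grown.
- *That Table 2 proves culture must be in hand at baseline.* It marks "Eligibility Screening" at baseline but has no smear or culture row in any column, so it shows little about when culture is read.

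**Conclusion.** The point holds in a limited form. On the plain reading of 2.2 with items 2 and 3 of 2.3.1, a newly diagnosed smear-positive patient qualifies only if anti-TB treatment has not started by the time culture grows. This is a poorly placed requirement with a safety and recruitment cost, and the treatment-naive restriction does not itself demand it: a treatment-naive patient can be enrolled at the smear.

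The conclusion assumes that item 2 means the definition in 2.2, and that the criteria must be met at recruitment, as 2.2 says. It would fall if the full protocol or the unseen figure allows allocation with culture pending; the eligibility text would then only need to say so. Confidence is moderate for that reason. It is worth correcting, because the correction is small and the possible consequence is untreated infectious disease.

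**What to change.** 1. Define item 2 at baseline as active lesions on chest CT plus a positive AFB smear.
2. Take a culture sample before treatment and record the result later as confirmation, not as a condition of allocation.
3. Keep item 3 and the treatment-naive population unchanged.
4. State that RIPE is never delayed or withheld to satisfy eligibility. If baseline assessments cannot be completed before RIPE is due, RIPE starts and the patient is not enrolled.
5. Set in advance how participants whose culture does not grow M. tuberculosis are handled. One option is to keep them in the randomised analysis and add a culture-confirmed sensitivity analysis; the choice is the sponsor's.

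**Cost.** A rewording of one criterion, one sentence on treatment timing, one recorded result and one handling rule. A few smear-positive participants without M. tuberculosis on culture may be randomised, which matters somewhat in a trial of 74. Baseline spirometry, with the 24 h without inhaled bronchodilators required in 2.6.1.1, must be arranged promptly after the smear, and some patients will be missed for that reason. If confirmation after allocation was always intended, items 1 and 2 only put that intention in writing.

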### 2.3 Participants

#### 2.3.1 Inclusion criteria

Patients who meet the following criteria will be included:1. Aged 40-75 years old;2. Meeting the Western medical diagnostic criteria and typing standards for active PTB;3. No use of steroids, anti-tuberculosis medications, or immunosuppressants, nor desensitization therapy administered within the past month;4. Documented comprehension of therapeutic protocols with voluntarily signed informed consent.

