#### 2.3.2 Exclusion criteria

Patients who meet any of the following criteria will be excluded:1. Patients with pneumothorax, pleural effusion, lung cancer, or other severe pulmonary comorbidities;2. Patients with severe cardiovascular/cerebrovascular, hepatorenal, or hematopoietic system disorders;3. Patients with psychiatric disorders;4. Patients with neoplastic diseases;5. Patients with congenital or acquired immunodeficiency.

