##### 2.6.1.1 Lung function assessment​​

Pulmonary function testing (PFT) will be conducted under standardized protocols to ensure data validity and reproducibility. Patients will be instructed to abstain from inhaled bronchodilators for at least 24 h prior to testing to avoid transient airway dilation effects. Resting heart rate will be maintained below 120 bpm to minimize cardiovascular interference during spirometry. Key spirometric parameters included:① Forced Vital Capacity (FVC)​​: Measures the total volume of air exhaled forcefully after maximal inhalation. Reduced FVC indicates severe obstructive conditions.② FVC%​​: The ratio of measured FVC to predicted values (based on age, sex, and height). Values < 80% suggest significant impairment.③ FEV1%​​: The percentage of predicted forced expiratory volume in the first second, reflecting airflow limitation severity. Classified as mild (≥80%), moderate (50%–79%), or severe (<50%).④ FEV1/FVC Ratio​​: Critical for distinguishing obstructive (ratio <0.7) and restrictive (ratio ≥0.7 with reduced FVC) disorders.

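### The inclusion list has no COPD item and, on its natural reading, admits previously treated tuberculosis, which contradicts the stated population of treatment-naive patients with tuberculosis and COPD

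*Protocol article*

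**What the plan says.** The aim, in section 1 of the protocol article, is to evaluate the pill in "treatment-naive adults with active PTB complicated by COPD". Section 2.2 repeats the disease part: "Study participants meeting the diagnostic criteria for active PTB with comorbid COPD will be recruited". Section 2.5.2 has both arms "concurrently receive guideline-concordant COPD management, including maintenance bronchodilator therapy", which presumes COPD in every participant.

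Section 2.3.1 then lists four inclusion criteria: age 40 to 75, active pulmonary tuberculosis, a restriction on earlier drugs, and consent. The disease item reads "Meeting the Western medical diagnostic criteria and typing standards for active PTB". The drug item reads "No use of steroids, anti-tuberculosis medications, or immunosuppressants, nor desensitization therapy administered within the past month".

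The lung-disease exclusion in section 2.3.2 is "Patients with pneumothorax, pleural effusion, lung cancer, or other severe pulmonary comorbidities". The only spirometric threshold for obstruction is in the outcome description of section 2.6.1.1, where the FEV1/FVC ratio is called "Critical for distinguishing obstructive (ratio <0.7) and restrictive (ratio ≥0.7 with reduced FVC) disorders".

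**The concern.** An eligibility list is what sites apply at the point of randomisation. Here it describes a wider population than the aim does, in two respects. COPD is not an entry item, and previous anti-tuberculosis treatment is restricted by a window where the aim says none at all.

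Both respects bear on interpretation. Several primary measures are tied to airflow obstruction or COPD: FEV1 percent predicted, FEV1/FVC, annual FEV1 decline, the COPD Assessment Test and exacerbation class. Patients without obstruction have little room to improve on the obstruction measures, and a mixed group would not support a conclusion about tuberculosis-associated obstructive disease. Previously treated patients may differ from treatment-naive ones in lung function and drug resistance, so a result from a mixture would not answer the question as posed. Neither mismatch can be repaired after enrolment without setting aside randomised patients from a trial of 74.

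**Working it through.** The plan states no figure on this point, so the check compares the text section by section.

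**COPD**

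| Place | What it requires or presumes |
|---|---|
| Section 1, aim | Active tuberculosis with COPD |
| Section 2.2, setting | Active tuberculosis with COPD; confirmation rules given for tuberculosis only |
| Section 2.3.1, inclusion | Active tuberculosis; COPD not named |
| Section 2.3.2, exclusion | Nothing that removes a patient without COPD |
| Section 2.5.2, background treatment | COPD treatment for all participants |
| Section 2.6.1.1, outcomes | FEV1/FVC below 0.7 as an interpretation note, not an entry rule |

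Taken alone, the lists in 2.3.1 and 2.3.2 are satisfied by a tuberculosis patient with normal or purely restrictive spirometry. Taken with 2.2, that patient should not be recruited. The sections therefore give different answers for the same patient. The confirmation sentence in 2.2 does not settle it, because it covers only the tuberculosis diagnosis: "Diagnostic confirmation of active PTB will adhere to the Chinese National Health Commission’s Health Industry Standard WS 288-2017".

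**Previous treatment**

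1. The aim says treatment-naive, meaning no earlier anti-tuberculosis treatment.
2. The drug item ends with a one-month limit. On the natural reading the limit governs every drug in the sentence, so a patient whose anti-tuberculosis drugs stopped more than a month ago qualifies.
3. No exclusion in 2.3.2 and no rule in 2.3.3 removes that patient.

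The aim and the list disagree, and no other section resolves it.

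**What dilution would do, as a hypothetical only**

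Section 2.4 gives 31 per group. It does not give the effect size or power behind that number. Assume a two-sided 5% test (the level in section 2.8), 80% power, and no effect at all in patients without COPD.

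- Implied standardised effect (normal approximation): d = √(2/31) × (1.960 + 0.842) = 0.254 × 2.802 = 0.71.
- With a fraction f of patients without COPD, the average effect is d(1 − f), power is Φ(2.802(1 − f) − 1.960), and the number per group that restores 80% power is 31/(1 − f)², rounded up.

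| f (assumed) | Power | Per group for 80% |
|---|---|---|
| 10% | 71% | 39 |
| 20% | 61% | 49 |
| 30% | 50% | 64 |

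If 90% power had been assumed (d = 0.82), the three power values would be 83%, 74% and 62%. Every input except the 31 and the 5% level is an assumption. The table shows the direction and scale of dilution if it occurred. It does not estimate what this trial will experience.

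**The case against.** The strongest reply is that COPD is a stated recruitment condition. Section 2.2 limits recruitment to patients with COPD, and section 2.5.2 treats everyone as having it. This stands as far as intent goes. A reader might infer from section 2.3.1 that patients without COPD will be enrolled and that the trial will lose power as a result. The documents do not support that step: 2.2 says the opposite about intent, and nothing gives a share of patients without COPD. The reply does not remove the contradiction, because the operative list still lacks the item.

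A second reply is that an article may leave the COPD diagnostic definition to the full protocol, and that the flow chart, which might show a COPD step, is not visible. This is fair about the missing definition, which is not by itself a finding. It does not excuse a printed, numbered list that goes into detail on desensitization therapy while omitting the disease that defines the trial.

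A third reply is grammatical. The one-month limit could attach to desensitization therapy alone, leaving anti-tuberculosis drugs barred without a time limit. That reading is possible and would agree with the aim, but it would also bar any lifetime use of steroids, so it is the less natural one. An item open to both readings still needs rewording.

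Finally, dilution would not be uniform. The primary outcomes also include FVC, breathlessness scales and imaging, and the introduction claims antitussive and immune effects that might appear without obstruction. This stands, and it is another reason not to rest the point on the power table.

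**Conclusion.** The point holds as a contradiction between sections. The inclusion list omits COPD, which the aim, setting and background treatment all take for granted. On its natural reading the list also admits previously treated patients, whom the aim rules out. The previous-treatment mismatch is not softened anywhere else in the document. The COPD mismatch is softened by section 2.2, which makes the intent clear.

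The consequence is that the list as printed can admit patients outside the stated population, and that the population to which the result applies is not fixed. A reader might go further and conclude that the trial is underpowered for this reason. The document gives no effect size, no power and no non-COPD share, so that conclusion is not available. The only assumption behind the verdict itself is the natural reading of the one-month limit, and the COPD half does not depend on it.

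**What to change.** 1. Add to section 2.3.1 an explicit COPD or airflow-obstruction criterion, confirmed on baseline spirometry read before allocation. Use whichever diagnostic criteria section 2.2 has in mind. The only cut-off in the article is FEV1/FVC below 0.7 in section 2.6.1.1, and the sponsor should say whether that is the one meant.
2. State whether the entry measurement is taken before or after bronchodilator. Section 2.6.1.1 has tests done after at least 24 hours without inhaled bronchodilators, so the condition cannot be left to inference.
3. Reconcile the drug item with the aim. Either require no previous anti-tuberculosis treatment, or remove the term treatment-naive from section 1 and limit the conclusion to the population actually admitted. If a one-month limit stays, say which drugs it governs.

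The cost is eligibility wording. Table 2 already schedules baseline spirometry, so no new test is needed. Screen failures may rise somewhat; the article gives no figures from which to say by how much.
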